### Datasets to be analysed, analysis populations

The final analysis will primarily rely on the data collected in the endline survey. Baseline variables will be used to 1) assess the extent to which balance was reached through the randomization and 2) create a set of control variables used in adjusted models.

### Primary Analysis

The primary analysis of program feasibility, acceptability and pre-post treatment analysis will be conducted directly be the PI of the parent study (GF) and the present sub-study (IFB) with support from the co-investigators. Effectiveness analysis will be done by the PI of the parent study (CF). This analysis will be intention-to-treat, and thus not adjust for protocol compliance.

#### Secondary Analyses

Secondary analysis focusing on subgroup effects as well as looking at secondary outcomes (mother-child relationship, functionality) will be conducted by the research team. We will also conduct per-protocol analysis to assess program impact among compliant caregivers.

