In Zambia, preliminary data collected by our research team suggest that 28% of mothers are in mental distress, one quarter of whom have severe symptoms. Like in many other LMICs, mental health resources are limited and mainly concentrated in a few psychiatric institutions focused on caring for severe illnesses such as schizophrenia. Most CMHDs remain undiagnosed and untreated as primary care (PC) systems are not equipped to address mental health needs of the population.

Evidence suggests that culturally adapted psychosocial programs, delivered by community health workers (CHWs), can be integrated in healthcare systems, increasing mental health access and workforce capacitywhile allowing the provision of evidence-based practice to treat mild to moderate common mental health disorders within the primary care setting along with other non-communicable diseases. However, two important obstacles hinder the implementation of psychosocial interventions within most sub-Saharan regions, including Zambia: 1) the lack of available culturally adapted evidence-based interventions tackling women with small children, 2) the treatment of those with severe symptoms.

First, even though the proven effectiveness of some psychosocial interventions in treating mild to moderate mental health symptoms, there are no tested treatments adapted to women in charge of young children living in low income settings. Second, around 30% of people with CMHD suffer severe symptoms which heavily impair the capacity to develop daily tasks including low performance in parenting activities, domestic duties and self-care routines including their capacity to engage in psychosocial intervention sessions. For those cases, regardless of the economic development of the country, pharmacological treatment is the first treatment option. However, even though there are generic medications, at a low cost and available in all areas of the world there is very little data on the effectiveness, training in use and management of psychotropic medication within the primary health system of low-income settings.

Our proposed project, lead by a clinical psychiatrist collaborating with a local team of clinicians and policy makers, will overcome these challenges by 1) testing a multi-level intervention that adequately identifies and treats women with mental health symptoms, no matter their severity

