## Primary and secondary endpoint

### Primary endpoint

The primary endpoint will be SRQ-20 = or < 7 6 months after enrollment in the trial and/or HSCL-25 <1.06 6 months after enrollment.

We will also collect data on attendance rates to assess feasibility and acceptability throughout the deployment of the intervention:

- Feasibility will be assessed by the percentage of participants completing 1 or more sessions of the intervention and through a focus group with the intervention providers.
- Acceptability will be evaluated using the percentage of participants completing the program (≥50% sessions completed) together with qualitative feedback from participants and providers through a semi-structured interview at the end of the intervention and participants’ feedback from a semi-structured interview at the end of the intervention.

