## Exclusion criteria

Women with active suicidal ideation (determined by Paykel scale^14^), severe substance use (ACOK-SUD >4),^15^ mania or psychotic symptoms^16^ will be excluded and referred to primary care provider or partnering psychiatrist (for emergency cases). Additionally, women planning to move in the next 6 months were excluded from the study.

We expect that around 70 caregivers will meet the inclusion criteria for the mental health feasibility study.

All eligible subjects will be randomized with probability of 0.5 to either treatment or control group. Randomization will be based on a random draw generated by the senior author (GF) using the Stata SE 16.0 statistical software package.

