### Comparator

The comparator (control group) will receive no intervention.

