## Description of statistical methods

First, we will begin with descriptive analysis of all data by site, using means, variances, quartiles, and graphical assessments of the distribution and skewness of the data. We will describe feasibility and acceptability measures at the participant level.

Then, we will proceed with a pre-post intervention analysis using the Hopkins Symptoms Checklist as a main outcome to compare mental health symptoms before and after receiving the intervention. Moreover, on a second phase, we will calculate effect sizes and trends of effectiveness between intervention group and the non-treated group from the parent trial using endline data from parent trial.

We will use standard linear regression models to assess the impact of the intervention arm on mother’s mental health and mother-child relationship. The intervention outcome variable will be SRQ-20 used as a dichotomous variable with the cutoff at seven. Separate models will be estimated with and without baseline covariates.

The feasibility, acceptability, and difficulties and successes in carrying out research and intervention activities will be explored through a mix-methods analysis including dosage analysis (attendance to the intervention’s sessions) and semi-structured interviews with the participants and focus group with intervention’s providers. The burden of completing the assessments and PM+FM on the time and effort of participants, satisfaction with the intervention, and barriers and facilitators to adherence will be explored through semi-structured interviews with all the participants enrolled in the intervention arm (including participants that have dropped out). Qualitative data resulting from the open-ended questions to participants and focus groups with WCHWs will be transcribed, coded and analysed using a thematic approach to inform on feasibility, acceptability, and explain the potential efficacy of the PM+FM intervention

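### The secondary per-protocol analysis of PM+FM would compare self-selected attenders with unselected controls; a complier-average effect based on random assignment is the better estimate of impact under uptake, provided its assumptions are stated

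*Protocol*

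**What the plan says.** The effectiveness analysis is by assignment. Under Primary Analysis the Protocol states: "This analysis will be intention-to-treat, and thus not adjust for protocol compliance". Secondary Analyses then adds: "We will also conduct per-protocol analysis to assess program impact among compliant caregivers". That sentence does not say who counts as compliant, who the comparator is, or how selection is handled.

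Other sections bear on how it would work:

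- **Allocation** (Exclusion criteria): "All eligible subjects will be randomized with probability of 0.5 to either treatment or control group".
- **Control condition** (Comparator): "The comparator (control group) will receive no intervention".
- **Attendance measures** (Primary endpoint): feasibility is the "percentage of participants completing 1 or more sessions of the intervention", and acceptability uses a threshold of at least half the sessions. Neither is named as the per-protocol definition.
- **Severity and attendance** (Scientific justification and rationale of study population): severe symptoms are said to impair women's daily functioning, "including their capacity to engage in psychosocial intervention sessions".
- **Covariates** (Description of statistical methods): "Separate models will be estimated with and without baseline covariates". The section on datasets and analysis populations says the baseline variables supply the controls for adjusted models.

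No complier-average or instrumental-variable analysis is mentioned.

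**The concern.** Randomisation makes the two arms comparable as wholes. It does not make the attending part of one arm comparable with the whole of the other. Because controls have no sessions to attend, the controls who would have attended cannot be picked out. The natural per-protocol contrast is therefore attenders against controls in general.

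If attendance is related to prognosis, the contrast mixes the effect of the sessions with the difference between women who attend and women who do not. The Protocol gives its own reason to expect such a relation, since it says severity reduces capacity to engage, and severity also bears on the SRQ-20 outcome.

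The Protocol also says the preliminary efficacy estimates will be used to size a larger trial. An effect among attenders that is partly selection could mislead that planning if it were used.

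**Working it through.** **1. The plan's own yardstick.** The sample size section states 100 analysed women per arm, with power 0.8 for a 20-point difference and 0.9 for 23 points. It gives no control prevalence, and sidedness is not stated. I assumed 0.60 and two-sided α = 0.05, and used the pooled-variance formula for two proportions:

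- 0.60 v 0.40: (0.20 − 1.96·√(2·0.25/100)) / √((0.24 + 0.24)/100) = 0.886, power 0.812.
- 0.60 v 0.37: the same formula gives power 0.908.

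The stated figures reproduce, so 20 points and 100 per arm are used as the scale below. The point does not depend on them.

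**2. Bias of attenders against all controls.** Let c be the share who comply, pC and pN the untreated endline prevalence in compliers and non-compliers, and δ the true effect in compliers (reduction in prevalence). Assume non-compliers get no effect.

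- Controls: c·pC + (1 − c)·pN.
- Compliers in the intervention arm: pC − δ.
- Difference: δ + (1 − c)·(pN − pC).

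The bias is (1 − c) × gap. The Protocol gives neither c nor the gap, so both are assumed, and no covariate adjustment is applied:

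| c | gap (points) | bias (points) |
|---|---|---|
| 0.80 | +10 | +2 |
| 0.80 | +20 | +4 |
| 0.60 | +20 | +8 |
| 0.60 | +30 | +12 |
| 0.50 | +20 | +10 |
| 0.80 | −10 | −2 |
| 0.60 | −10 | −4 |
| 0.50 | −10 | −5 |

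A positive bias favours PM+FM. With no gap there is no bias.

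**3. Complier-average effect.** The intention-to-treat difference is c·δ, so dividing by c returns δ, provided assignment affects the outcome only through attendance.

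**4. Simulation.** 20,000 trials, 100 per arm, control prevalence 0.60, c = 0.60, gap 20 points (pC = 0.52, pN = 0.72):

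| True δ | Attenders v all controls, mean (SD) | Complier-average, mean (SD) |
|---|---|---|
| 0 | 8.0 (8.2) | −0.2 (11.8) |
| 20 | 27.9 (7.8) | 19.8 (11.5) |

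With no true effect, the attender comparison rejects in 16.9% of trials at a nominal 5%. The intention-to-treat test rejects in 5.3%.

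**5. Choice of threshold.** Suppose 60% attend at least half the sessions with δ = 20, and 30% attend some but fewer, with an effect of 5 or 10 points.

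- Intention-to-treat: 0.6·20 + 0.3·5 = 13.5, or 0.6·20 + 0.3·10 = 15.0.
- Half-of-sessions threshold: 13.5/0.6 = 22.5, or 15.0/0.6 = 25.0, against a true 20. Partial attenders' benefit is credited to compliers.
- One-session threshold: 13.5/0.9 = 15.0, or 15.0/0.9 = 16.7. Each equals the true average effect among all attenders.

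**6. Width.** Relative to intention-to-treat, the interval is wider by about 1/c: 1/0.8 = 1.25 to 1/0.6 = 1.67.

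**The case against.** The strongest reply is that the Protocol gives one sentence, and that the compliance threshold, analysis set and estimator are often left to a SAP, which is not available here. It is true that a comparison with all controls is inferred, not written. A reader might take it as the stated method, but the text does not say so. The point survives because the sentence does commit to a per-protocol method for measuring impact among compliant women, and a no-intervention control arm offers no compliant controls to compare them with.

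Second, the planned covariates include severity, the one confounder the Protocol itself points to, which is measured at baseline by SRQ-20 and HSCL-25. Adjustment would shrink the figures above, which are for an unadjusted contrast. It would not deal with unmeasured motivation or time, and models without covariates are planned as well.

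Third, a reader might infer that the bias must favour PM+FM. The severity remark makes that plausible, but women who recover early may stop attending, which would reverse the sign. The documents do not settle it.

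Fourth, a reader might infer that a complier-average effect answers the same question free of bias. It does not:

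- With a one-session threshold, the estimand is the effect among women attending at least one session, not among programme completers.
- It needs the exclusion restriction. Engagement calls and home visits (Study design), or referral with subsidised medication (Experimental intervention), could break it if they reach non-attenders and differ between arms.
- It needs the randomised controls. The statistical methods section refers to a non-treated group from the parent trial. If that group is wider than the randomised controls, assignment is no longer a valid instrument.
- Missing outcomes are not imputed (Handling of data), which can bias either estimator.

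Last, precision is poor. Study design expects around 70 eligible women. At 35 per arm the SD scales by √(100/35) = 1.69, to about 19–20 points. This argues for modest claims from any estimate of effect under uptake; it does not make the attender comparison valid.

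**Conclusion.** The point holds as a weakness in a secondary analysis. In practice the per-protocol comparison would set self-selected attenders against unselected controls, and it is biased whenever attendance is related to prognosis. The size is 2 to 12 points for assumed compliance of 60–80% and an assumed gap of 10–30 points before adjustment. It is −2 to −4 points over the same compliance range if the gap is −10. These inputs are illustrations, not Protocol figures.

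A reader might go further and conclude that the trial's effectiveness result is compromised. The Protocol does not support that: effectiveness is analysed by intention-to-treat, and efficacy is described as exploratory. A complier-average effect uses the randomisation and is the better estimate of impact under uptake, conditional on the exclusion restriction and on the randomised controls being the comparator.

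**What to change.** Replace the per-protocol sentence in Secondary Analyses with a complier-average causal effect, specified as follows:

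- Two-stage least squares, with random assignment as the instrument. This fits the linear models already planned for the dichotomised SRQ-20.
- The randomised controls as comparator, not a wider parent-trial group.
- Attendance of at least one session as treatment received.
- Adjustment for baseline SRQ-20, entered as a score because every eligible woman is above the cutoff.
- A statement that the estimand is the average effect among women attending at least one session. It should add that this rests on the exclusion restriction, which engagement contacts or referral and subsidised medication reaching non-attenders could violate.
- Any comparison restricted to attenders, or to women with at least half the sessions, reported as descriptive. A half-of-sessions threshold should not be used as treatment received, because partial attenders would violate the exclusion restriction.

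Intention-to-treat stays as the effectiveness analysis.

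The cost is a change of wording and one further model, with no new data, since attendance is already recorded. The price is precision. The interval is about 1.25–1.67 times as wide as the intention-to-treat interval at 80–60% compliance. It is also wider than the per-protocol interval: SD about 11.5–11.8 against 7.8–8.2 points at 60% attendance and 100 per arm.

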#### Interim analyses

No interim analysis is foreseen.

#### Deviation(s) from the original statistical plan

Any deviations from the original statistical plan will be reported in the Methods section of the final project report.

## Handling of data

Missing data will arise when a participant refuses to answer a question or complete the part of the examinations. Missing data may also arise is a participant drops out of the study. All participants are informed that their participation is completely voluntary and that they may refuse to answer any of the questions asked and can stop the evaluation at any time as well as discontinue participation at any time without any consequences. Missing data on covariates will be imputed using multiple imputations using chained equations. Missing outcome data due to sample attrition will not be imputed; however, we will conduct and report analyses examining the extent to which attrition differed across treatment conditions.

# Duties of the Investigator

## Investigator’s confirmation

### Local regulations / Declaration of Helsinki

This research project will be conducted in accordance with the protocol, the Declaration of Helsinki, KFPE principles for transboundary research as well as all national legal and regulatory requirements.

### Notification of safety and protective measures (HRO Art. 20)

see 10.2.

### Serious events (HRO Art. 21)

see 10.2.

## Project management

The PIs of the project will be responsible for management and coordination of the project.

# Ethical considerations

## Independent Ethics Committee (IEC)

All study documents will be reviewed by the EKNZ in Switzerland as well as the ethics board at the University of Zambia in Lusaka.

## Evaluation of the risk-benefit ratio

Given that the interventions are primarily designed to support mothers, adverse outcomes seem unlikely.

## Participant information and consent

Trained interviewers will explain the nature of the study to the participant, and answer all questions regarding this study, prior to obtaining informed consent.

Withdrawal and discontinuation

Participation is completely voluntary and participants may withdraw from the study at any time or may refuse to answer any questions without having repercussions on their participation. If the participant decides to withdraw from the study they may request that their information already obtained will be destroyed and electronic data deleted and not be used for evaluation.

## Registration of clinical trial

This trial will be registered at www.clinicaltrials.gov. We will also submit this study protocol for publication.

## Participant confidentiality

All records will be collected electronically and stored on a secure server. For analysis, all personal information will be removed, and a unique Participant Number (e.g. 2738) assigned to each participant. The Investigators will keep a separate confidential enrolment log that matches identifying codes with the participants’ names and residencies, preferably in the Trial Master File.

## Participants requiring particular protection

NA

## Damage coverage

NA

## Participant compensation

All participants will be given a small present (a piece of soap or something similar) to thank them for their time spent with interviews at the end of the interview. No incentives will be provided to attend to the intervention sessions.

## Other aspects

NA.

# Quality control and quality assurance: description of measures

All study staff will be carefully trained by the research team to ensure highest possible data quality. Data will be collected electronically, and reviewed for consistency on a weekly basis.

All field staff undergoes training in ethics in research.

## Risk management

### Risk identification, assessment and mitigation

The proposed interventions do not pose any known risk to participating women. Similarly, if women are not interested in attending the intervention, they can simply inform study staff they are no longer interested in receiving them.

### Study-specific preventive measures

NA.

## Monitoring

Both baseline and endline surveys will be monitored electronically through the Survey CTO software package.

## Audits and inspections

The study documentation and the source data/documents are accessible to the ethics committees and auditors/inspectors at all times. All involved parties will keep the participant data strictly confidential.

## Confidentiality, data protection

Project data is only accessible to authorized personnel who require data to fulfil their duties within the scope of the research project. On the eCFRs and other project specific documents, participants are only identified by a unique participant number. De-identified data will be made publicly available after the publication of the trial.

## Translations - Reference language

The reference language for all study documents is English. ICFs and CRFs (baseline and endline survey questionnaires) will be translated to local language.

## Storage of biological material and related health data

No biological material will be collected as part of this project. All data collected will be coded. Codes can be linked to personal identifying information including first and family name, address, phone number, e-mail address, village leader name. This will be stored using the Survey CTO server and only senior research team members (project manager, data manager and PI’s) affiliated to the study will have access to this database. Our project does not include the storage of bio-specimens.

# Dissemination of results and publication policy

## Dissemination to scientific community; incl. lead in publications

Data analysis will lead to a series of synthesizing reports and publications in peer-review scientific journals for which all principles of data safety and protection are considered, and any results are presented in a fully anonymized manner.

## Information of community and policy makers

This study will be conducted in close collaboration with the **Zambian Ministry of Health (MoH).** [name] will be part of the advisory board along with local team of clinicians and policy makers.

Progress will also be shared through the MoH’s health sector mental health technically working group quarterly meetings.

